# Exploring mechanisms of fatigue during repeated exercise and the dose dependent effects of carbohydrate and protein ingestion: study protocol for a randomised controlled trial

**DOI:** 10.1186/1745-6215-15-95

**Published:** 2014-03-26

**Keywords:** Nutrition, Recovery, Carbohydrate, Protein, Performance

## Abstract

**Background:**

Muscle glycogen has been well established as the primary metabolic energy substrate during physical exercise of moderate- to high-intensity and has accordingly been implicated as a limiting factor when such activity is sustained for a prolonged duration. However, the role of this substrate during repeated exercise after limited recovery is less clear, with ongoing debate regarding how recovery processes can best be supported via nutritional intervention. The aim of this project is to examine the causes of fatigue during repeated exercise bouts via manipulation of glycogen availability through nutritional intervention, thus simultaneously informing aspects of the optimal feeding strategy for recovery from prolonged exercise.

**Methods/Design:**

The project involves two phases with each involving two treatment arms administered in a repeated measures design. For each treatment, participants will be required to exercise to the point of volitional exhaustion on a motorised treadmill at 70% of previously determined maximal oxygen uptake, before a four hour recovery period in which participants will be prescribed solutions providing 1.2 grams of sucrose per kilogram of body mass per hour of recovery (g.kg^-1^.h^-1^) relative to either a lower rate of sucrose ingestion (that is, 0.3 g.kg^-1^. h^-1^; Phase I) or a moderate dose (that is, 0.8 g.kg^-1^.h^-1^) rendered isocaloric via the addition of 0.4 g.kg^-1^.h^-1^ whey protein hydrolysate (Phase II); the latter administered in a double blind manner as part of a randomised and counterbalanced design. Muscle biopsies will be sampled at the beginning and end of recovery for determination of muscle glycogen resynthesis rates, with further biopsies taken following a second bout of exhaustive exercise to determine differences in substrate availability relative to the initial sample taken following the first exercise bout.

**Discussion:**

Phase I will inform whether a dose–response relationship exists between carbohydrate ingestion rate and muscle glycogen availability and/or the subsequent capacity for physical exercise. Phase II will determine whether such effects are dependent on glycogen availability *per se* or energy intake, potentially via protein mediated mechanisms.

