### Trial objectives

This research trial will investigate the relationships between carbohydrate intake, muscle glycogen metabolism and exercise capacity during a repeated bout of physical exercise. It will explore whether the effect of carbohydrate ingestion is causal between muscle glycogen availability and/or endurance capacity, and if this relationship is linked to the carbohydrate fraction *per se* or simply to an energy intake surplus. Thus, a replacement of a fraction of the carbohydrate with a different macronutrient (whey protein hydrolysate) matched in energy content will be examined to assess if whey protein hydrolysate co-ingestion provides a distinct benefit over carbohydrates alone in relation to muscle glycogen storage and/or the capacity for subsequent exercise. Specifically, we aim to accomplish the following objectives: (i) to examine whether a dose–response relationship exists between rates of carbohydrate (sucrose) ingestion and muscle glycogen availability following short-term recovery and/or the capacity for subsequent exercise; and (ii) to explore the potential protein-mediated effects upon muscle glycogen resynthesis and/or the capacity for a subsequent exercise bout with the ingestion of whey protein hydrolysate.

The use of the disaccharide sucrose was chosen on the basis of its potential positive contribution to liver and/or muscle glycogen resynthesis by virtue of equimolar amounts of glucose and fructose. Following exhaustive exercise, sucrose and glucose ingestion seem to elicit similar muscle glycogen resynthesis rates
[24]. However, resting intravenous
[25,26] and oral ingestion
[27] studies indicate that fructose preferentially stores liver glycogen relative to glucose, while glucose infusion favours muscle glycogen resynthesis. Given the importance of both liver and muscle glycogen replenishment during short-term recovery and subsequent endurance capacity
[28], sucrose was deemed a preferable source of carbohydrate to undergo predominant hepatic metabolism (that is, fructose) to optimise liver glycogen resynthesis alongside a glucose source to maximise muscle glycogen storage
[29].

An important factor determining the rate of muscle glycogen resynthesis is insulin-mediated glucose uptake by the muscle cells
[8]. A proposed mechanism for the potential benefit of protein co-ingestion in enhancing the rate of glycogen storage is the synergistic effect of this substrate on insulin secretion

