### Trial design

The methods described here stem from a wider project titled ‘Macronutrient ingestion, Muscle glycogen and Post-Exercise Recovery’. Both trial phases described herein have been approved by the National Health Service (NHS) South West 3 Research Ethics Committee (REC) with an allocated reference number: 09/H0101/82. The project was subsequently registered as a clinical controlled trial (ISRCTN 87937960).

Phase I of testing will address objective (i) by way of a non-randomised repeated measures design. The chosen trial design for Phase I is based on the premise that a lower rate of sucrose ingestion will mediate sub-optimal recovery, thus resulting in impairment in exercise capacity relative to a higher rate of sucrose intake, as has been previously reported in a similar investigation
[21]. It was, therefore, assumed that participants would run longer when the higher sucrose treatment was administered. Accordingly, a non-randomised design would allow not only an investigation of the metabolic environment at the point of fatigue during the low versus high sucrose treatments, but also at the time point in the high sucrose treatment coincident with the onset of fatigue during low sucrose treatment. Indeed, previous studies have adopted a similar approach to investigate mechanisms through which carbohydrate supplementation enhances the capacity for both cycling
[37] and running
[38] modes of exercise. In addition, participants will be fully familiarised with a trial (see experimental protocol) that will be identical to the main procedures and, therefore, diminishing any order effects. This will consequently improve the reliability of the performance measure that would enable the detection of small but worthwhile intervention effects
[39].

The second phase (Phase II) of testing will address objective (ii) by adopting a randomised double-blind cross-over experimental design.

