#### Experimental design

The global design of the trial includes comparisons of two nutritional interventions during each distinct phase of testing. A minimum of two weeks wash-out period will be allowed between each main trial to avoid any carry-over effects. The independent variable will be the precise nutritional intervention applied during the short-term recovery period. This involves the provision of 0.3 g.kg^-1^.h^-1^ and 1.2 g.kg^-1^.h^-1^ of carbohydrate in the form of sucrose solutions in Phase I of testing and a 1.2 g.kg^-1^.h^-1^ sucrose versus an 0.8 g.kg^-1^.h^-1^ sucrose + 0.4 g.kg^-1^.h^-1^ whey protein hydrolysate in Phase II of the project. All treatments will be provided in equal volumes (10 ml.kg^-1^.h^-1^) and will be matched in sodium and potassium composition. The test beverages will also be matched in flavour (vanilla extract). Sample analyses of both treatments underwent screening by an independent institution (HFL Sport Science, LGC Ltd., Teddington, Middlesex, UK) to confirm the absence of any contaminants such as banned anabolic steroids and stimulants including noradrenaline, Tetrahydrogestrinone (THG) and 3,4-methylenedioxymethamphetamine (MDMA). A full description of the treatment composition is provided in Table 
1.

**Table 1 T1:** Nutritional information of the supplements provided in phase I and phase II of the trial

	**Low sucrose**	**High sucrose**	**Moderate sucrose + whey protein hydrolysate**
Sucrose (g/L)	30	120	80
Lactose (g/L)	-	-	≤3.5^a^
Protein (g/L)	-	-	40
Fat (g/L)	-	-	≤2.2^a^
Sodium (g/L)	0.38	0.38	0.38
Potassium (g/L)	0.47	0.47	0.47
Calcium (g/L)	-	-	0.2
Magnesium (g/L)	-	-	0.01
Phosphorous (g/L)	-	-	0.12
Chloride (g/L)	-	-	0.15
Energy (kcal/L)	120	480	480

^a^Assay unable to detect values below this number. The caloric content for fat and lactose was therefore assumed negligible.

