#### Participants

The chosen target population for the research trial will be healthy non-smoking recreationally active men and women who include endurance training in the form of running as a central component (≥2 hours/week) of their training regime. The chosen age range for participation will be 18 to 48 years old. The research trial aims to recruit sixteen participants (eight in each phase of testing) from the University of Bath campus and surrounding sporting clubs by way of public advertisement and personal communication. These individuals will all be trained (as evidenced both by their self-reported training volume and also measures of maximal oxygen uptake during preliminary testing). Upon volunteering, the participants will be initially briefed in writing followed by a verbal explanation of the protocol and the pre-requisites set for satisfactory inclusion on their first visit to the laboratories to ensure their full understanding before the investigation. The target population sample will be free from any condition that either poses undue personal risk or introduces bias into the experiment (as determined by each participant’s responses to baseline health screening). In relation to eumenorrheic female participants, all measurements will be conducted at least three and at most ten days after the onset of menses (that is, the follicular phase) to ensure low levels of circulating female hormones and, therefore, minimise any measurement errors associated with the menstrual cycle. Each participant will be required to attend the Physiology Research Laboratory at the University of Bath on four occasions. These include: (i) a preliminary visit; (ii) a familiarisation visit; and (iii) two main trials completed on separate days.

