### Statistical analysis

While the primary outcome measure in these experiments is the rate of muscle glycogen resynthesis/degradation, this variable is highly reliable relative to other outcomes and, accordingly, this consistency results in sample size estimates requiring only four or five participants (thus justifying the use of typically six or eight participants in most studies in this field). It was, therefore, deemed appropriate to base sample size estimates on secondary, less reliable, outcome measures. In this case, exercise capacity exhibits the highest between subject variability and our previous work that contributes directly to the rationale for this study observed a difference between the high sucrose and moderate sucrose plus whey protein supplements under investigation here of 7.5 minutes, with a standard deviation of differences of 5 minutes
[21]. Based upon these data, it can be estimated that a sample size of seven would be appropriate even to provide a 90% power to detect such effects on these more variable secondary outcomes using a two tailed paired *t*-test.

A paired *t*-test will be used to compare between treatments for the primary and secondary outcomes of the study (that is, glycogen resynthesis/degradation and run times to exhaustion). A two-way linear mixed model with repeated measures (beverage × time) will be employed to analyse the repeated experimental conditions. Mauchly’s test will be used for sphericity. Where asphericity is assumed, the Greenhouse-Geisser correction will be used for epsilon <0.75 and Huynh-Feldt will be adopted for less severe asphericity. Where significant F values are found a Bonferroni step-wise correction will be employed to determine the location of the variance
[62]. Simple summary statistics will be used to inform interesting questions related to certain metabolites (for example, plasma glucose) following each feeding strategy and during the subsequent exhaustive bout. Statistical procedures were performed using commercially available software (IBM SPSS version 20.0, SPSS Inc., Chicago, IL, USA) and significance is set at an alpha level of 0.05. All results will be reported as the mean ± standard deviation (SD) of the mean unless stated otherwise.

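### Phase II can estimate the effect of swapping sucrose for whey protein at equal energy, but a null result would not show that energy intake is what matters

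*Protocol article*

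**What the plan says.** The abstract's Discussion states that "Phase II will determine whether such effects are dependent on glycogen availability" per se or on energy intake, and adds that protein may mediate this. Trial objectives puts the same question as whether the relationship is tied to the carbohydrate fraction "or simply to an energy intake surplus". Objective (ii) in that section is more modest: it sets out to explore protein-mediated effects.

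Phase II has two arms in a "randomised double-blind cross-over experimental design". The comparison is 1.2 g/kg/h "sucrose versus an 0.8 g.kg^-1^.h^-1^ sucrose + 0.4 g.kg^-1^.h^-1^ whey protein hydrolysate in Phase II of the project", with the second drink "rendered isocaloric via the addition of 0.4 g.kg^-1^.h^-1^ whey protein hydrolysate". Table 1 gives 480 kcal/L for both. The target is "sixteen participants (eight in each phase of testing").

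Statistical analysis compares treatments on glycogen and run time by paired t-test at alpha 0.05. The sample size is calculated with a two-tailed test from "a difference between the high sucrose and moderate sucrose plus whey protein supplements under investigation here of 7.5 minutes", with an SD of differences of 5 minutes. On reporting it says: "All results will be reported as the mean ± standard deviation (SD) of the mean unless stated otherwise".

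**The concern.** Because the drinks are matched for energy, the hypothesis that only energy matters predicts the same result in both arms. The planned test looks for a difference. Failing to find one is not evidence that none exists, least of all when the interval is wide enough to contain the effect the trial was sized on.

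A second problem remains however precise the data are. The arms differ in two components, and Trial objectives itself describes a route by which whey hydrolysate could raise glycogen storage through insulin. Equal results could therefore mean that energy drives recovery, or that a protein-specific effect makes up for less sucrose.

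At stake is what the Phase II paper may conclude. An imprecise null could be presented as support for the energy explanation, and the stated aim would invite that reading.

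**Working it through.** **Inputs.** Table 1: 120 g/L sucrose, against 80 g/L sucrose plus 40 g/L protein. Experimental design: 10 ml/kg/h of either drink. Statistical analysis: difference 7.5 min, SD of differences 5 min, two-sided alpha 0.05, 90% power, n = 7. Participants: eight per phase. Assumed here, because the plan gives no smaller effect: true differences of 5, 3.75 and 2.5 min.

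**1. Energy and dose.** The table's low-sucrose column (30 g/L, 120 kcal/L) implies 4 kcal/g. Then 120 × 4 = 480 and (80 + 40) × 4 = 480 kcal/L, so the drinks are isocaloric. At 0.01 L/kg/h the doses are 0.01 × 120 = 1.2 sucrose, against 0.01 × 80 = 0.8 sucrose plus 0.01 × 40 = 0.4 protein (g/kg/h).

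**2. The plan's own sample size.** Standardised effect 7.5/5 = 1.5. Exact power of the two-sided paired t-test (noncentral t, n − 1 df, noncentrality 1.5√n) is 83.3% at n = 6, 90.8% at n = 7 and 95.1% at n = 8. The stated seven reproduces. This is power to find a difference of 7.5 min.

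**3. Precision with eight.** Standard error 5/√8 = 1.77 min. The expected 95% CI half-width is t(0.975, 7) × 1.77 = 2.365 × 1.77 = 4.18 min. An observed difference of 4 min with SD 5 would be non-significant, with 95% CI 4 ± 4.18, or −0.2 to 8.2 min. That interval contains both zero and the 7.5 min planning effect.

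**4. Chance of a non-significant result when a difference exists (n = 8, SD 5).**

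| True difference (min) | Power | Non-significant |
|---|---|---|
| 7.5 (planning value) | 95% | 5% |
| 5 (assumed) | 68% | 32% |
| 3.75 (assumed, half) | 45% | 55% |
| 2.5 (assumed, one third) | 23% | 77% |

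The smallest difference detectable with 80% power is 5.8 min.

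**5. Is eight simply too few?** Power of two one-sided tests at 0.05 each, with true difference zero, SD 5 and n = 8 (simulated, 1,000,000 draws): 97% for a margin of ±7.5 min, 63% for ±5 and 28% for ±3.75. The answer depends on the margin. The widest margin is weak grounds for similarity. For the 4-min example the 90% CI is 4 ± 1.895 × 1.77 = 4 ± 3.35, or 0.65 to 7.35 min. That lies inside ±7.5, yet it excludes zero.

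**6. What each outcome could support.**
- Sucrose drink better: the amount of carbohydrate matters beyond energy.
- Protein drink better: protein has an effect of its own.
- Run time differs while glycogen is similar: this also needs a no-difference conclusion, on glycogen.
- No difference: energy alone, protein offsetting the lower sucrose, or imprecision. No Phase II arm gives 0.8 g/kg/h sucrose alone or with non-protein energy. The only lower-energy arm (0.3 g/kg/h) is in Phase I, which is not randomised and is planned with its own eight participants.

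**7. Glycogen.** No SD or effect size is given for the primary outcome, so steps 3 to 5 cannot be repeated for it.

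**The case against.** The best defence has several parts, and much of it stands.

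- *No text says a null will be read as equality.* Correct. A reader might infer that the protocol plans to treat p > 0.05 as proof of the energy hypothesis. It does not say so; this is a foreseeable risk. The mean ± SD convention is descriptive and does not rule out intervals for differences.
- *Margins and intervals belong in a SAP that is not shown.* Accepted: their absence is not the point. The attribution claim and the two arms are stated in the article, and no SAP can make those arms separate energy from protein.
- *The abstract hedges, and objective (ii) only explores.* True, and the planned two-sided test suits objective (ii). But the abstract's verb is *determine*, and Trial objectives opposes carbohydrate to energy alone, so the stated purpose goes further than the objective.
- *Under the planning effect a null is rare.* Yes, about 5%. The 55% rests on an assumed smaller effect.
- *The figures concern the secondary outcome.* Yes. Glycogen is described as highly reliable and may be estimated more precisely, though how much cannot be checked.

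Two further readings are tempting. One is that eight participants are too few. The documents do not support this as the core fault: eight exceeds the seven required for the planned test and would give 97% power for equivalence within ±7.5 min. The other is that an arm must be added. That is a design preference, and the objection to the claim is met by narrowing the claim.

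**Conclusion.** The point holds as an overstated conclusion. Phase II can estimate the effect of replacing part of the sucrose by whey hydrolysate at equal energy, and a clear difference either way would be informative. It cannot establish that energy intake is what matters, for two separate reasons: a non-significant difference test does not show equality, and equal results would not distinguish energy from a compensating protein effect.

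The second reason needs no arithmetic. The size of the first, for run time only, is an expected 95% CI half-width of about 4.2 min against a planning effect of 7.5 min, and a 55% chance of missing an assumed true difference of 3.75 min. These figures take the plan's SD of 5 min at face value with eight complete pairs. At an assumed SD of 7.5 min the half-width would be 6.3 min.

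**What to change.** 1. In the abstract's Discussion and in Trial objectives, restate the Phase II aim as the effect of replacing 0.4 g/kg/h sucrose by whey protein hydrolysate at equal energy, in line with objective (ii). Add that energy and protein effects are not separable with these two arms.
2. In Statistical analysis, report the paired mean difference with its 95% CI for glycogen and for run time, in addition to mean ± SD. State that a non-significant result is inconclusive and will not be read as similarity or as support for the energy hypothesis.

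Do not add an equivalence margin of ±7.5 min: it equals the full planning effect and would label the 4-min example similar.

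The cost is some rewording and one interval per outcome, with no new data and no change to treatment. The downside is a less ambitious headline, and some null results become inconclusive. Trial status reports that Phase II is recruiting and collecting data, so the wording should be settled before its results are analysed.

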**Trial registration:**

ISRCTN87937960.

## Background

It is well established that during prolonged moderate to high intensity exercise, carbohydrate is primarily utilised to support energy metabolism due to its efficiency and expeditious availability to support the energetic requirements of such activities
[1-3]. In humans, the majority of endogenous carbohydrate is stored as glycogen in the muscle and liver
[4] with the capacity to sustain muscle contractions at the aforementioned exercise intensities being highly dependent on the availability of this glycogen at these sites
[5,6]. The physiological mechanisms responsible for these observations appear to involve several inter-related factors including: maintenance of euglycaemia and an attenuation of central nervous system fatigue; glycogen sparing; and reduced exercise-induced strain
[7].

Recovery following exercise is mainly determined by the time required to replenish the depleted glycogen stores and ingesting sufficient carbohydrate (6 to 10 grams of carbohydrate per kilogram of body mass per day) is necessary to restore both glycogen depots and the capacity for repeated physical exertion
[8-10]. Conversely, when periods of recovery are limited (≤8 hours), such as various training and competition scenarios, neither of the aforementioned processes can be entirely restored
[11]. This underpins the importance of identifying nutritional strategies to maximise recovery and restoration of exercise capacity in concurrence with manifestations of fatigue during a repeated exercise bout. To date, nutritional research concerning recovery from exercise has been based on the assumption that similar fatigue mechanisms will operate during repeated exercise within hours of an initial bout, so has understandably focused on strategies to accelerate muscle glycogen resynthesis. While much is now known about the amount, type and timing of nutrient intake that can facilitate muscle glycogen storage and/or the capacity for repeated physical exertion
[11], little evidence exists to demonstrate a link between these variables.

When examining these variables independently, it appears that muscle glycogen resytnhesis is augmented during recovery as opposed to a placebo
[12,13] and a dose–response relationship exists between carbohydrate intake and muscle glycogen resynthesis until reaching a threshold of 1.2 grams per kilogram of body mass per hour of recovery (g.kg^-1^.h^-1^)
[11]. In addition to the amount of carbohydrate provided, muscle glycogen storage is primarily influenced by the energy content irrespective of the macronutrient composition
[14]. Consequently, the glycogenic properties of carbohydrate may be related to the increased energy content or mediated metabolic responses (hyperinsulinaemia) rather than the presence of carbohydrate fraction *per se*. Therefore, several studies were implemented to explore the efficacy of mixed macronutrient ingestion during recovery and repeated exercise, particularly carbohydrate-protein supplementation
[15]. The culmination of the results suggests that increasing the amount of carbohydrate is sufficient to maximise glycogen resynthesis rates and restore endurance capacity more completely
[11], although some indicate a distinct advantage of protein co-ingestion
[16-18]. Further investigation is required, particularly during running-based exercise, to elucidate the efficacy of protein co-ingestion on restoration of muscle glycogen during limited recovery and the potential ergogenic effects upon subsequent endurance capacity.

Based on the above information, increasing carbohydrate intake during short-term recovery can accelerate muscle glycogen resynthesis. Nevertheless, endurance capacity may not concurrently improve
[19,20]. Only one investigation reported an enhanced capacity for repeated exercise following limited recovery in response to higher carbohydrate intake
[21]. Few investigations have been conducted to examine the role of muscle glycogen during a subsequent exercise bout
[17,22,23], and none examined muscle glycogen degradation during a repeated exhaustive exercise bout. In accordance, glycogen availability may not play a fundamental role in contrast to an initial exercise bout whereby fatigue is intimately associated with glycogen depletion
[5]. Different fatigue mechanisms may take place, and muscle glycogen metabolism during a subsequent exhaustive exercise bout following short-term recovery remains to be examined.

